### Intervention

2.5

Study subjects are randomly assigned to one of the following three groups: Experimental Group 1 (EG1), Experimental Group 2 (EG2) or the Control Group (CG) through a computer randomization system using the statistical program Epidat V4.2.

Once the subjects have been informed of the entire study procedure and have signed the informed consent form (Annexes I, II) this information is expanded in the Supplementary Material, they will be evaluated before starting treatment. Subjects will receive an initial evaluation based on clinical parameters and follow-up medical records. The data will be collected by an evaluator and integrated into our research databases using an Excel spreadsheet.

Both experimental groups will receive an invasive physiotherapy protocol (one weekly session) applied to the sternocleidomastoid and/or levator scapulae muscles, in addition to the standard physiotherapy program. The intervention will be conducted over four weeks, with a total of 20 sessions (five per week), following rehabilitation medicine guidelines for this condition. This standardization ensures consistency in treatment exposure and enhances reproducibility of the protocol.

The therapeutic exercise program will be delivered under the supervision of trained physiotherapists. Exercises will be performed in progressive phases, with adjustments in intensity, resistance, and volume according to predefined progression criteria. Details of the exercise program are summarized in Table 1.

**Table 1 T1:** Relationship between standard physiotherapy procedure and intervention.

Intervention procedure	Physiotherapy intervention	Description	Duration/Repetitions	Frequency	Subjects
Experimental group	EPI	Hong technique on localized MTrPs (ECOM and/or Levator scapulae)	1× week	1 day for 4 weeks	GE_1_
	Dry needling	Hong technique on localized MTrPs (ECOM and/or Levator scapulae)	1× week	1 day for 4 weeks	GE_2_
Standard physiotherapy procedure (GE + GC)	Thermotherapy + analgesic electrotherapy	Microwave or thermotherapy techniques combined with TENS.	15 min	5 days for 4 weeks	GE + GC
	Massage therapy	Friction maneuvers, kneading, and manual stretching of the muscle and affected area.	20 min	5 days for 4 weeks	GE + GC
	Manual therapy	- Deep friction massage - Contraction- relaxation technique passive - Stretching and self-stretching	10 min	5 days for 4 weeks	GE + GC
			2–3 repetitions		
	Active mobility joint range	- Free active mobility exercises in all planes of motion of the affected joints	2–3 repetitions per movement	5 days for 4 weeks	GE + GC

Currently there are several devices to perform the EPI technique, we will use the EPI XM Omega model for our study (Figure 2). Before performing the technique, the area to be treated will be disinfected and cleaned with 2% chlorhexidine, and gloves will be put on. Next, the areas of hyperalgesia will be located by palpation, and then, using ultrasound, different areas of degeneration will be searched for in that localized point. To apply the current, an intensity of 3 milliamps (mA) will be applied for 5 s according to the established protocol for the technique (130, 132, 133). This method will be performed three times on each target point found. Performing the technique creates an inflammatory response in the tissue, which can last from 5 to 7 days to a maximum of 15 days. After two weeks, it can be confirmed that there is no inflammatory infiltrate at the site of application (130, 144, 147, 157).

**Figure 2 F2:**
[figure not shown]
EPI Model: XM Omega.

In the case of dry needling treatment on a myofascial trigger point located in the sternocleidomastoid and/or levator scapulae muscles of the affected area, the aforementioned asepsis and hygiene measures must also be followed beforehand.

The modified Hong technique (quick entry and exit) is performed, seeking a local spasm response—at least one response, indicating that the treatment is more effective than without it (62). Once the needle is withdrawn, pressure should be applied to the puncture site where the technique was performed for 1–2 min to prevent bruising. This is done as post-needle care to prevent post-needle pain and promote hemostasis.

The procedure at the control group will include standard physical therapy following the progression criteria based on clinical guidelines for patients with whiplash syndrome (14), treating the sternocleidomastoid and/or levator scapulae muscles with a frequency of 5 weekly sessions for 4 weeks. The two professionals performing the procedure are professionals with more than ten years of experience in invasive techniques. Before the start of the trial, the therapists participated in a training and protocol standardization session to ensure consistency in the application of the procedures. Treatment fidelity measures were implemented throughout the study, and any protocol deviations were systematically recorded. The professionals and evaluators are different.

### Outcomes measures and tools

2.6

The initial assessment includes a clinical history-taking interview. We will strive to ensure the sample data are homogeneous at the start of the study, ensuring there are no significant differences in demographic, medical, and other variables at the outset.

#### Primary outcome measures

2.6.1

##### Intrafibrillar blood flow

2.6.1.1

After suffering a traffic accident and consequently suffering from CLS, the cervical vertebrae may become blocked. This leads to a slight lack of blood supply to the brain, compromising its vascularization due to the compression of the vertebral artery, producing a feeling of instability (158). The arteries considered most important in the neck, according to the study by Martinez Medina (159), since blood flow to the brain occurs primarily through two arteries: the vertebral artery, located in the posterior region, and the carotid artery, located in the middle and anterior part of the neck. Compression of these main arteries can cause cervical dizziness. These are associated with various symptoms such as dizziness, tension in the neck, nausea, vertigo, and photophobia or sensitivity to light (158).

The vertebral artery may be compressed in some areas along its path to the skull or at the entrance to it, where it must bend to avoid the occipital condyle. If the position of this condyle varies due to the tension of the cervical muscles, it is obvious that the artery is slightly compressed. As for the carotid artery, it may be compressed in its fascial sheath common to that of the anterior cervical muscles or at the entrance to the skull (158).

Ultrasonography, also known as musculoskeletal ultrasound, is an important diagnostic tool that has evolved both technologically and in terms of understanding pathologies affecting soft tissues such as the skin, muscles, bursae, tendons, and ligaments, among others (160).

In this study, the term intrafibrillar blood flow is used in an operational sense to describe local muscle microcirculation assessed indirectly through Doppler ultrasound. Although this imaging technique does not measure blood flow within muscle fibers *per se*, it provides information on the perfusion of small-caliber vessels adjacent to the fibers. These measures are interpreted as indirect indicators of the metabolic state of the tissue and its capacity for recovery. By adopting this approach, we aim to complement traditional patient-reported outcomes with objective physiological parameters that may reflect tissue-level healing processes.

This type of examination is performed on a digital device with a high-frequency linear array transducer (47). Furthermore, color Doppler can be used to assess small vessel hypervascularity (slow flow) in the inflamed synovial tissue of the studied structures (160).

This instrument is used to measure intrafibrillar blood flow, which is the volume of blood pumped in a unit of time. Measurements are expressed in milliliters per second (ml/s) or liters per minute (l/min). In turn, the speed at which the flow moves, that is, the distance traveled in the unit of time, is measured in centimeters per second (cm/s) or meters per second (m/s) (161).

##### Muscle fiber elasticity

2.6.1.2

There are three types of muscle: skeletal muscle, cardiac muscle, and smooth muscle, focusing on skeletal muscle.

Its unique physiology determines a series of characteristics unique to this tissue. Its most interesting property is the ability to contract under electrical stimulation derived from voluntary nerve control, which leads to changes in its structure and mechanical properties (162). Over the last century, numerous investigations have been conducted on changes in the mechanical properties of muscle tissue using elastography, specifically quantitative elastography (Shear-Wave: SWE). Recent literature has shown promising results in the evaluation of various traumatic and pathological conditions in various musculoskeletal tissues, including muscles, ligaments, and nerves (163).

Elastography or sonoelastography (SE) uses an electronic device to generate an acoustic pulse that produces tissue deformation through a transverse shear wave (163). This device is an imaging technique based on the differentiation of the elasticity of healthy tissue compared to pathological tissue, which can be measured based on the tension applied to the tissue. The elastic properties of soft tissue depend on their molecular conformation and structural organization, both microscopically and macroscopically (163). It also allows the characterization of the mechanical and intrinsic properties of muscle tissue: edema, atrophy, and fatty infiltration (163). In this way, it measures the velocity (m/s) of the waves generated by the acoustic pulse at all points in the tissue studied, which allows the stiffness and elasticity of the tissue to be expressed in units of pressure (kilopascals) (163).

Elastography is obtained when a color parametric image expressing the velocity of tissue deformity is superimposed on the grayscale ultrasound anatomical image. These tissues tend to develop greater deformity, while those with greater stiffness show less deformity (163). More technically, elastography is an imaging technique that distinguishes the stiffness of affected tissue, always comparing it with normal tissue, and codes it in color.

The technique displays two distinct colors: red and blue. Red indicates a stiffer tissue, while blue indicates a softer tissue. Yellow or green indicates a tissue with intermediate characteristics (163, 164).

#### Secondary outcomes measures

2.6.2

##### Pain

2.6.2.1

Pain is a quantitative variable characterized by being a subjective phenomenon, and there are many ways to classify it (165). We will use the numerical rating scale (NRS) (166), which consists of a numbered scale from 1 to 10, where 0 is the absence and 10 is the greatest perceived intensity. The patient will be asked to mark the number that determines the intensity of the symptom.

Another quantitative variable of pain is the pressure pain threshold (PPT) (167). A pressure algometer will be used to measure this variable. This instrument measures “the minimum amount of pressure necessary to cause discomfort at a given point” (168). Measurements are expressed in kg/cm^2^, with the maximum being 10 kg/cm^2^. This instrument has been shown to be valid, reliable, and reproducible for quantifying pain sensitivity in patients with myofascial pain syndrome (169).

We will use these two instruments, since the NRS presents subjective and emotional factors of the patient while the algometer is more quantitative and is associated with nociceptive weakness based on a noxious stimulus (170).

##### Disability

2.6.2.2

According to the World Health Organization (WHO), the generic term “disability” covers all impairments, limitations in performing activities and participation restrictions, and refers to the negative aspects of the interaction between a person with a health condition and contextual factors of that person such as environmental and personal factors (171). To assess disability, we will use the scale called Whiplash Disability Questionnaire (WDQ) (Annex III); this information is expanded in the Supplementary Material. It is the first instrument designed by Hoving et al. (172) for patients with whiplash syndrome, based on the neck disability index (NDI), which includes items related to areas of life, personal care and work, as well as those related to pain perception. To measure the degree of disability in whiplash syndrome of the participants, we will use this questionnaire in its Spanish version (173). This questionnaire consists of 13 items, scored from 0 to 10 points, where 0 corresponds to no pain/not at all and 10 corresponds to I can't/Always.

A summary of the research outcomes and measurement instruments is shown in Table 2.

**Table 2 T2:** Relationship between variables and measuring instruments.

Variables	Instrument/Tool	Type
Intrafibrillar blood Flow	Doppler ultrasound examination	ml/sg or L/min
Muscle fiber elasticity	Elastography	Pressure unit (kilopascals)
Pain	Numeric scale (NS)	Numeric
	Pressure algometer	Kg/s
Disability	Whiplash Disability Questionnaire (WDQ)	Numeric

### Data collection procedure, monitoring, and management

2.7

During data collection, the information will be anonymized, and all data from the clinical history, anamnesis, and the various study variables will be compiled. Once all the information has been gathered, an individual palpatory assessment of the sternocleidomastoid and/or levator scapulae muscles will be performed, along with a set of tools and instruments for measuring variables.

The procedure for taking variable measurements and evaluations will be carried out before the start of the program (Pre-Test), four weeks after the completion of the intervention (Post-Test).

Both the initial assessment (Pre-Test) and the four-week measurements (Post-Test) will be performed by an evaluator unaware of the nature of the intervention, at a designated location, with easy access for the patient and prior appointment confirmation.

The data will be added to the database created for this purpose and managed by the principal investigator. A data collection notebook will be used as supporting material and will be used for statistical analysis.

The results of the research will be presented as a summary of the outcome measures, along with the estimated effect size and its precision. Statistical analysis will be performed according to the intention-to-treat principle using SPSS software, with statistical significance set at *p* < 0.05. Descriptive statistical analysis of the different variables will be performed. Results will be evaluated by comparing differences between groups using linear mixed model statistics and the *t*-test to test the hypothesis that group means are or are not significantly different from each other.

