**Objective:**

The primary objective of this study is to evaluate the effectiveness of percutaneous intratissue electrolysis (EPI) on intrafibrillar blood flow and muscle fiber elasticity compared to deep dry needling (DN) and standard physiotherapy. Secondary objectives include the assessment of perceived pain, disability, and clinical outcomes at follow-up.

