Intratissue percutaneous electrolysis (EPI) is an invasive minimally physiotherapy technique that applies galvanic current through a needle to induce a controlled inflammatory response and promote tissue repair. By combining mechanical and electrical stimuli, EPI has demonstrated effectiveness in reducing pain and disability in tendinopathies and other musculoskeletal pain conditions, with favorable outcomes reported in the short, medium, and long term. Moreover, when adverse events are reported, they are generally infrequent and mild, although safety reporting remains limited and should be further standardized in future clinical trials (128–130). Designed by Sánchez Ibáñez in 2003, its application requires rigorous asepsis and ultrasound guidance to ensure safety and accuracy (98, 99, 101, 131).

Galvanic current is administered by means of an active cathode (needle) and an anode, with doses determined by Faraday's Law: high intensities and short times for regeneration; low intensities and long times for analgesia (99). It is contraindicated in cases such as unstable epilepsy, open wounds or metallic implants (83). EPI has shown pain reduction and functional improvement with moderate evidence, especially in chronic tendinopathies combined with eccentric exercise (99, 132, 133). However, some studies have found no relevant differences with respect to placebo or DN (134–137). It has also been evaluated in conditions such as lateral epicondylalgia, temporomandibular dysfunctions and rotator cuff pain, where it has outperformed DN in some cases (130, 133, 138–140), although more research is needed to validate these results due to methodological variability (85, 130, 133, 141–147).

The primary objective of this research is to evaluate the efficacy of two physiotherapeutic interventions - percutaneous intratissue electrolysis (PIE) and deep dry needling (DDN) - in adults with WAD after traffic accidents and to see if there is an improvement in intrafibrillar blood flow and muscle fiber elasticity compared to a standard physiotherapy protocol. Secondary objectives include the evaluation and analysis of perceived pain, disability, and long-term variable clinical outcomes.

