### Sample size

2.3

To date, there are no studies reporting on the use of deep dry needling and/or percutaneous intratissue electrolysis in patients who have suffered from whiplash syndrome, so that this randomized, blinded clinical trial will provide evidence for the effect size.

To calculate the population size, we used data published by the Directorate General of Traffic (DGT), updated in 2020, which identified 242 patients who were victims of traffic accidents in the city of Melilla. The Al-Therapy Statistics tool will be used for the sample calculation (https://www.ai-therapy.com/psychology-statistics/sample-size-calculator). Therefore, we will use a sample size of (*n* = 36) with a proportional distribution for each study group (GE1 group = 12 + GE2 group = 12 + Control group = 12) with an expected loss ratio (R = 15%) and a confidence interval (CI = 95%), this information is expanded in the Supplementary Material.

However, this calculation does not provide sufficient statistical power. A more robust estimation can be derived from validated clinical parameters reported in the literature: a minimum clinically important difference (MCID) of 2 points on the Numeric Rating Scale (NRS) for pain (151–153), a standard deviation of approximately 2.5 (154), and a pre–post correlation ranging between 0.5 and 0.7 (155, 156). Based on these assumptions, the required sample size would range from 20 to 31 participants per group (60–93 in total) to ensure adequate power.

Since the present study will include only 36 participants, it should be explicitly characterized as a pilot randomized controlled trial, designed to assess feasibility, refine procedures, and provide preliminary effect size estimates to guide the design of a fully powered clinical trial.

For the development of this research, a non-probabilistic intentional sampling will be used for the convenience of the study, due to the characteristics of the subjects to be studied. Strategies to ensure adequate inclusion of participants who meet the target sample size include collaboration with a health center affiliated with the UNESPA agreement on healthcare resulting from traffic accidents, rehabilitation physicians, and physiotherapy teams.

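### One between-group hypothesis is given to both a mixed model and a t-test at p < 0.05 with neither deciding, and the primary contrasts differ between the Abstract and the Introduction

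*Protocol article*

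**What the plan says.** Section 2.7 puts the between-group question to two methods: "using linear mixed model statistics and the *t*-test to test the hypothesis that group means are or are not significantly different from each other". The threshold is common to everything: "with statistical significance set at *p* < 0.05". The same section says that "Statistical analysis will be performed according to the intention-to-treat principle using SPSS software" and promises effect sizes with their precision.

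The design has three equal arms, "GE1 group = 12 + GE2 group = 12 + Control group = 12" (section 2.3). Section 2.6.1, headed "Primary outcome measures", contains two outcomes: intrafibrillar blood flow and muscle fiber elasticity.

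The primary objective appears twice. The Abstract's is the "effectiveness of percutaneous intratissue electrolysis (EPI) on intrafibrillar blood flow and muscle fiber elasticity compared to deep dry needling (DN) and standard physiotherapy", and the hypothesis in the Abstract's Methods repeats those two comparisons. The Introduction instead evaluates EPI and DN together, looking for "improvement in intrafibrillar blood flow and muscle fiber elasticity compared to a standard physiotherapy protocol".

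Section 2.3 also concedes that 36 patients do not give sufficient power and describes the trial as a pilot for feasibility and preliminary effect sizes.

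**The concern.** A t-test compares two groups, so three arms need up to three of them. The text names neither the pairs nor the role of the t-test beside the mixed model. If the two methods disagree, nothing in the article says which one counts.

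The conflict in objectives makes this worse. EPI against DN is primary in the Abstract and absent from the Introduction's primary objective; DN against standard physiotherapy is the reverse. With either outcome able to count as success, a reader of the final report could not tell which of several p-values was meant to decide, and the choice could be made after the data are seen.

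**Working it through.** **1. The two objectives side by side**

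| Contrast | Abstract | Introduction |
|---|---|---|
| EPI vs standard | primary | primary |
| EPI vs DN | primary | not included |
| DN vs standard | not included | primary |

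Only EPI vs standard is common to both. An analysis plan that picked either set would depart from one published objective.

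**2. Error rate when nothing differs.** Inputs: 12 per arm, three arms, two outcomes, alpha 0.05 (all from the article). Two-sided tests and normal data are assumed, and the correlation between the outcomes is not given, so it is varied from 0 to 0.8.

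Treating tests as independent, the chance of at least one significant result is 1 − 0.95^k: 14.3% for k = 3 and 26.5% for k = 6. This overstates it, because pairwise contrasts share arms. Simulation of the actual layout (40,000 trials per setting) gives:

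| Tests at 0.05 | Correlation 0 | 0.5 | 0.8 |
|---|---|---|---|
| 3 pairwise, one outcome | 12% | 12% | 12% |
| 3 pairwise, both outcomes | 22.9% | 21.3% | 18.4% |
| 2 contrasts with a common arm, both outcomes | 17.4% | 16.1% | 13.9% |
| One three-arm overall test per outcome | 9.8% | 9.0% | 7.7% |

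Every reading in which either outcome may count exceeds 5%.

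Counting only false results that favour EPI (over DN or over standard, on either outcome), a separate run of 100,000 trials gives 8.8%, 8.1% and 7.0% at correlations 0, 0.5 and 0.8. For a single contrast on one outcome that rate would be 2.5%.

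**3. The article's own sample-size range.** Section 2.3 gives 20–31 per group from 2 points on the pain scale, SD 2.5 and pre–post correlation r = 0.5–0.7. Change-score SD = 2.5·√(2(1 − r)) = 2.50 at r = 0.5 and 1.94 at r = 0.7. Assuming 80% power, a two-sided t-test needs 31 and 20 at alpha 0.025 (an exact match). At alpha 0.05 it needs 26 and 16, or 31 and 19 after dividing by 0.85 for the 15% loss. The article states neither the alpha nor the power behind the range. It concerns pain, a secondary outcome, so it is no evidence of error control for the primary outcomes.

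**4. What baseline adjustment is worth.** Same pain inputs, 12 per arm, two-sided alpha 0.05, noncentral t:

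- Post-score t-test: SD 2.5, power 47%.
- Change-score t-test: SD 2.50 to 1.94, power 47% (r = 0.5) to 68% (r = 0.7).
- Baseline-adjusted: SD = 2.5·√(1 − r²) = 2.17 to 1.79, power 58% to 74% (21 degrees of freedom, one spent on the covariate).

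This is illustration only. The article gives no SD or correlation for blood flow or elasticity.

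**The case against.** The best reply is that this is a self-declared pilot reported in a condensed article. Error control is not the purpose of a pilot, and a rule for sharing alpha is something a statistical analysis plan, not shown here, would normally hold. That stands as far as it goes: a missing alpha rule on its own would be no finding. It does not reach the conflicting objectives or the two unranked methods, which are in the published text. Nor does the pilot label remove the superiority hypothesis in the Abstract or the significance threshold in 2.7.

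A second reply is that the t-test may be meant as pairwise follow-up to the mixed model. That is possible, but the article does not say so, and unadjusted follow-up at 0.05 is the case simulated.

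Four stronger readings are tempting and are not supported:

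- A reader might infer that the t-test ignores baseline and breaks intention-to-treat. The article never says that raw post-scores are used or that patients with missing values are dropped. It is a risk, given an expected 15% loss. A mixed model fitted to post-baseline values would also gain nothing from a patient with no post-baseline value.
- A reader might infer that the 18–23% is the chance of a false claim for EPI. It also counts DN vs standard and results in the opposite direction; the EPI-favouring rate is about 7–9%.
- A reader might add a second post-baseline visit and reach 35–39% (visit correlation 0.5, outcome correlation 0 to 0.5). That depends on the three-month visit, which the Abstract lists and section 2.7 does not.
- A reader might blame the inflation on running two methods. The figures above come from contrasts and outcomes; the effect of choosing between the mixed model and the t-test was not measured, because the model is not specified.

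**Conclusion.** The point holds as a specific inconsistency in the published text: two unranked methods for one hypothesis at a single threshold, and two primary objectives that share only one contrast. If pairwise t-tests at 0.05 are what is meant, familywise error is about 12% on one outcome and 18–23% over both. This rests on 12 per arm, two-sided tests, normal data, outcome correlation between 0.8 and 0, and either outcome counting as success. A rule that both outcomes must succeed would need no split of alpha across them, but none is stated. The pilot status lowers the stakes of strict error control. It does not tell the reader which contrast or method is primary.

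**What to change.** 1. Reconcile the Abstract's objective and hypothesis with the Introduction, so that one primary objective and one set of primary contrasts remains.
2. Drop the t-test as a separate test. Make one linear mixed model, adjusted for the baseline value and using small-sample degrees of freedom (Kenward–Roger or Satterthwaite), the deciding analysis, and take all pairwise contrasts from it.
3. Reconcile the assessment times and name one primary time point. The Abstract has assessments after four weeks of intervention and three months post-intervention; section 2.7 places the post-test four weeks after the intervention ends and lists no three-month visit.
4. Then choose. Either follow the pilot status in 2.3 and report every contrast as an estimate with a 95% confidence interval and no significance claim; or, if testing is kept, name one primary outcome or apply Holm over the primary outcomes and contrasts.

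The change is to wording. The price of keeping several tests is a stricter threshold for each: Holm's first step is 0.05/4 = 0.0125 for two outcomes and two contrasts. On the illustrative pain inputs, the baseline-adjusted analysis at 0.025 has 45–63% power with 12 per arm, against 47% for an unadjusted post-score t-test at 0.05, so adjustment recovers most or all of a two-way split. A finer split costs more: at 0.05/6 = 0.0083 power falls to about 29–46%. That favours either the estimation route or a single named primary outcome and contrast.

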**Methods:**

This single-blind randomized clinical trial will be conducted in patients residing in Melilla with whiplash syndrome due to traffic accidents. Participants will receive interventions targeting the sternocleidomastoid and/or levator scapulae muscles. Assessments will be conducted at baseline, after four weeks of intervention, and at three months post-intervention to evaluate medium-term effects. Our hypothesis is that EPI will produce greater improvements in the study variables compared to DN and standard physiotherapy.

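### Two primary outcomes in three arms are tested at a flat 0.05 with no error control or success rule: a 9–23% chance of a false-positive primary result, depending on which comparisons count

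*Protocol article*

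**What the plan says.** Section 2.7 fixes one level, "with statistical significance set at *p* < 0.05", and evaluates results by "comparing differences between groups using linear mixed model statistics and the *t*-test". The stated purpose of the t-test is to "test the hypothesis that group means are or are not significantly different from each other". The section does not say how the mixed model and the t-test relate.

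Section 2.6.1 lists two primary outcomes, blood flow by Doppler and elasticity by elastography, and ranks neither above the other. Section 2.3 sets the arms: "GE1 group = 12 + GE2 group = 12 + Control group = 12".

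The comparisons of interest differ by place. The Abstract's objective is the effectiveness of EPI "on intrafibrillar blood flow and muscle fiber elasticity compared to deep dry needling (DN) and standard physiotherapy", and its hypothesis is that "EPI will produce greater improvements in the study variables compared to DN and standard physiotherapy". The Introduction instead sets both needling techniques against control, looking for "improvement in intrafibrillar blood flow and muscle fiber elasticity compared to a standard physiotherapy protocol". Together these cover all three pairs.

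Section 2.3 also concedes that 36 participants give too little power and says the study should be characterised as a pilot.

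**The concern.** A t-test compares two means, so three arms imply several tests for each outcome, and there are two primary outcomes. The article names no key contrast, no order of testing, no overall test that must succeed first and no adjustment. Nor does it say whether one significant result supports the hypothesis or whether EPI must beat both comparators on both outcomes.

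The two ends of that range are very different trials. If any significant result counts, the chance of a false claim is well above the stated 5%. If every result must be significant, the trial will seldom confirm a hypothesis that is true. A reader of the eventual report could not tell from this text which standard applied.

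**Working it through.** **1. The plan's own figure.** The article states no family-wise error rate. Its nearest figure is in Section 2.3: "the required sample size would range from 20 to 31 participants per group", from a 2-point difference on the pain NRS, SD about 2.5 and pre–post correlation r of 0.5 to 0.7. No alpha and no power value are given for it. For a two-sample t-test on change scores, SD of change = 2.5 × √(2(1 − r)):

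- r = 0.5: SD 2.5, d = 2/2.5 = 0.80
- r = 0.7: SD 1.94, d = 2/1.94 = 1.03

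| Setting (80% power, two-sided) | r = 0.5 | r = 0.7 |
|---|---|---|
| alpha 0.05, no loss | 26 | 16 |
| alpha 0.05, divided by 0.85 for the stated 15% loss | 31 | 19 |
| alpha 0.025, no loss | 31 | 20 |

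The range of 20 to 31 is matched exactly by the last row and within one participant by the second. It does not reveal an intended alpha.

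**2. Number of primary tests at one visit.** All pairs: 2 outcomes × 3 pairs = 6. EPI contrasts only: 2 × 2 = 4. If the tests were independent, the chance of at least one p < 0.05 under the null would be 1 − 0.95⁶ = 26.5% and 1 − 0.95⁴ = 18.5%. These are only reference values, because contrasts share arms and the outcomes may be correlated.

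**3. Simulation.** 200,000 null trials per setting, 12 per arm, t-tests at 0.05. Tests are taken as two-sided from the wording, since sidedness is not stated. The correlation between the two outcomes is an assumption.

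| Chance of at least one significant primary result | corr. 0 | 0.3 | 0.5 | 0.7 |
|---|---|---|---|---|
| All three pairs, both outcomes | 22.7% | 22.4% | 21.4% | 19.9% |
| EPI vs DN and EPI vs standard only | 17.1% | 16.8% | 16.2% | 15.1% |
| Pairs tested only after a significant three-group F test | 9.6% | 9.5% | 9.2% | 8.5% |

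One outcome alone with three pairs gives about 12%. At correlation 0.9 the three rows fall to 16.9%, 12.9% and 7.3%, still above 5%. With 10 per arm (12 × 0.85 = 10.2), the first row is 23.0% at correlation 0 and 21.5% at 0.5.

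**4. Source of the excess.** With 0.05/6 for each of the six tests, the simulated family-wise rate is 4.4%, 4.3% and 4.0% at correlation 0, 0.5 and 0.7. The inflation therefore comes from the unadjusted level.

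**5. The opposite reading.** If EPI must beat both arms on both outcomes, each at 0.05, power is 9–18% at an assumed true d of 0.8. The article gives no effect size for either primary outcome.

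**The case against.** **A separate analysis plan may settle this.** Section 2.7 is a short summary and never says that tests are unadjusted. It is fair to say that the text cannot show the rule will be chosen after the data; a reader might infer that, but nothing here supports it. The point still stands, because the article does more than stay silent: it commits to a level, a test and a superiority hypothesis, and that combination does not control the error rate.

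**The highest rate is only one reading.** This stands. A reader might take 20–23% as the trial's false-positive rate, or about four times nominal. The article does not fix all three pairs as the primary family. The hypothesis names only the EPI contrasts, and listing the mixed model before the t-test leaves a gated reading open. Testing two visits separately would raise the all-pairs rate to about 35–37% (assumed between-visit correlation 0.6), but Section 2.7 lists only pre-test and post-test, although the Abstract adds three months.

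**The sizing might seem to show that alpha 0.025 was intended.** A reader might infer this from the exact match in step 1 of the working. It does not hold: alpha 0.05 with the stated 15% loss gives 31 and 19, no alpha or power is stated, and the range sizes pain, a secondary outcome.

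**It is a pilot.** Section 2.3 says so, and Section 2.7 promises effect sizes with their precision. This lowers the consequence. It does not remove the defect while the efficacy objective, the superiority hypothesis and the significance test remain.

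**Conclusion.** The concern holds as a conditional statement. With two primary outcomes, three arms, a flat 0.05 and no success rule, the chance of at least one significant primary result under no true effect at one visit is about 20–23%, 15–17% or 9–10%, according to whether all pairs, only the EPI contrasts, or F-gated pairs are tested. The figures rest on 12 per arm, two-sided tests, any single success counting, and an outcome correlation of 0 to 0.7. None of the three readings brings the rate down to 5%.

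Given the pilot status this should be fixed, but it does not invalidate the design.

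**What to change.** In Section 2.7, before any comparative data are seen, choose one of two routes.

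**Controlled testing.** Name one primary visit, which also means reconciling the visit schedule in the Abstract with that in Section 2.7. Define the primary family as EPI vs DN and EPI vs standard physiotherapy on both primary outcomes: four tests. State whether the mixed model or the t-test supplies the p-values. Apply Holm at family-wise two-sided 0.05. Claim support only for each contrast and outcome that passes; the full hypothesis on the primary outcomes is supported only if all four pass. Report DN vs standard, other visits, NRS, PPT and WDQ as estimates with 95% confidence intervals and no significance claim.

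**Estimation only.** In keeping with the pilot label, drop significance claims and report every contrast as an estimate with a 95% confidence interval.

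Either route takes a few sentences. The cost of Holm is power: its first step uses 0.05/4 = 0.0125, so per-test power at an assumed d of 0.8 with 12 per arm falls from about 47% to 25%. Passing all four tests would be no more likely than the 9–18% shown in the working. Estimation loses only the confirmatory claim.
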